### Secondary outcomes

The following are the secondary outcomes of the study:
Characterization of the processes in the drugstores and drugstores/pharmacies. The measurements will be performed only at baseline (T0) before the intervention.Implementation of the ambulatory (outpatient) pharmacy services in the drugstores and drugstores/pharmacies. The measurements will be performed only at baseline (T0) before the intervention.Level of pharmacy staff satisfaction with the continuing education program. The measurements will be performed only on the intervention group pharmacy staff after completing the follow-up (T12).Level of satisfaction of patients or caregivers with ambulatory (outpatient) pharmacy services. The measurements will be performed at baseline (T0) before the intervention and 12 months (1 year) after completing the follow-up (T12)

### Data collection

Data will be collected between December 2018 and December 2019, conducted over 12 months of intervention delivery and follow-up. The data obtained in this study will be registered in an electronic database. The effectiveness of the continuing education program will be assessed before and after the intervention. The same questionnaires will be used in T0 and T12 for the pharmacy staff and the patients or caregivers. An additional measurement will be made for the intervention group 12 months after the end of the follow-up time in order to evaluate the effects of the educational intervention over time. All measuring instruments will be reviewed and adjusted by a group of 10 experts. Three different sessions will be carried out, in which the questionnaire will be presented, and the experts will be asked for their opinions regarding the relevance of the content of the items (content validity).

#### Community pharmacy staff competencies (knowledge, skills, and attitudes)

For the measurement of knowledge, a self-applied questionnaire of 50 multiple-choice questions (4 possible answers) with only one answer was constructed, and it will be categorized as correct or incorrect. The questionnaire will have the following topics: (1) pharmaceutical terminology and basic pharmacology, (2) pharmaceutical legislation, (3) technical and administrative management of the pharmacy, (4) communication and health education from the pharmacy, (5) good practices of dispensing and proper use of medicines, (6) pharmacovigilance from the pharmacy, and (7) pharmaceutical intervention on some common diseases in pharmacy (depression, anxiety disorder, sleep disorders, and pain management).

For the measurement of skills and attitudes, a self-applied questionnaire of 100 questions or performance criteria was constructed, which will be evaluated according to the frequency in which it will perform. For this purpose, a Likert scale will be established with four possible options: never (1), sometimes (2), usually (3), or always (4) that evaluate the following competencies—(a) provision of patient care: initial contact with the patient, medical prescription, medication needs, medication reconciliation, medication supply, use of guidelines and protocols, drug specifications, drug interactions, information about medications and patient education, additional activities, identification of drug-related problems, patient care, and evaluation of results; (b) personal: personal organization, practical communication skills, teamwork, and professionalism; (c) problem-solving: access related to information, knowledge, information analysis, and monitoring the patient; and (d) management and organization: clinical management and pharmacological safety, service provision, acquisition, and satisfaction of the services offered.

For the construction of the questionnaire, a search of reference documents, associations, and working groups in this area was carried out at an international level, focused on the guidelines and recommendations related to the proper functioning of the ambulatory pharmaceutical services and drugstores and drugstores/pharmacies. The international reference documents of the International Pharmaceutical Federation (FIP) and the World Health Organization [16, 17, 24] were used as sources of review, in which a minimum set of competencies was described within the different frameworks of professional performance. Additionally, different labor competency frameworks in different countries such as England, Ireland, and Australia [25–27] and the regulations in Colombia associated with the labor competencies of the pharmacy staff were reviewed. Additionally, a structured review was conducted on the measurement and evaluation of labor competencies, with the following MeSH terms: “Professional Competence” OR “Health Knowledge, Attitudes, Practice” AND “Pharmacists.” Finally, the results of the reviews were considered. The adjustment and revision of the instrument were carried out with a group of experts from the areas of healthcare pharmacy, research, and teaching. In total, 993 bibliographic references were identified with the search strategy, selecting nine articles that globally assessed competencies in 4 countries: Croatia, Australia, England, and Serbia [25–33].

#### Simulated patient technique

The simulated patient technique will be used to evaluate the skills and attitudes of the pharmacy staff in the dispensation and the information supply for the correct use of drugs with fiscalized substances. The simulated patients will be trained to represent and act coherently and accurately predetermined disease, specifically in pain management. Before carrying out the visits, the simulated patients who were previously trained would sign an informed consent in order to guarantee the confidentiality of the information collected. The pharmacy staff will not know at any time that the simulated patient is not real. A questionnaire will be constructed which will assess the following: (1) the drug dispensed, (2) the use of tools to provide information, and (3) the information provided on drug precautions and recommendations. The questionnaire will evaluate the minimum information that the pharmacy staff should provide to patients according to the indications, precautions, and recommendations for the use of the drug and the disease that will simulate (tramadol and lower back pain) [34, 35]. Both the information and the dispensing process must be carried out under the regulatory requirements.

#### Characteristics of the event and simulated patient

Patient with an average age of 20 years will go to the drugstores or drugstores/pharmacies with a medical formula of tramadol 100 mg/ml bottle 10 ml drops (10 drops/8 h), prescribed by a doctor, for a week-long back pain associated with physical exertion. There will be training performed for simulated patients. Additionally, a first dispensation will simulate (simulated patient will use tramadol for the first time). To guarantee the quality and validity of the data, one of the researchers will transport the simulated patients to all the visits and thus will validate the process and the storage of the data.

#### Characterization of the processes in the drugstores and drugstores/pharmacies

A self-designed questionnaire will be constructed from the requirements of Colombian pharmaceutical regulations and different bibliographical references [36, 37] to characterize the processes associated with the use the drugs with fiscalized substances, including compliance with the regulations, and to determine the level of risk perception with of use of these drugs in the pharmacy staff.

#### Implementation of the ambulatory (outpatient) pharmacy services

A questionnaire will be constructed from the requirements of Colombian pharmaceutical regulations and different bibliographical references [36, 37] for the measurement and degree of implementation of ambulatory (outpatient) pharmacy services.

#### Level of pharmacy staff satisfaction with the continuing education program

A questionnaire will be constructed from different bibliographical references [36, 38] to evaluate the satisfaction level of pharmacy staff about the continuing education program. A 5-point scale ranging from excellent, good, satisfactory, needs improvement, and unacceptable will be used in the questionnaire.

#### Level of satisfaction of patients or caregivers with the ambulatory (outpatient) pharmacy services

A questionnaire will be constructed from the requirements of Colombian pharmaceutical regulations and different bibliographical references [39, 40] to evaluate the information and education services on the appropriate use of drugs. The questionnaire will inquire about the following: (1) establishment information, (2) patient or caregiver information, (3) medication information, (4) assessment of the information and education service, and (5) qualification of the care received. The satisfaction of the care received in drugstores or drugstores/pharmacies will be evaluated with a 5-point scale ranging from excellent, very good, good, satisfactory, regular, and bad

To promote the retention of participants and complete follow-ups, the pharmacy staff will receive a physical certificate when he/she completes each module of the virtual course, which is part of the intervention (intervention group). Additionally, at the end of the follow-up time, all pharmacies of the intervention and control groups will receive a physical certificate that guarantees that said establishment participated in the study.

### Data management

Only one of the researchers involved in the trial will have access to the data entry. The data will be controlled by a second investigator to avoid errors in transcription. The data will be stored in a database. Those involved in this study will be the only ones with access to the information. We will back up the database every week in 2 different computers to protect the information. All the questionnaires will be carried out in physical format, except the questionnaire that evaluates the satisfaction of the continuing education program in the intervention group, which will be sent by means of an electronic survey, and the information will be stored online in Excel format.

### Statistical methods

Baseline and demographic characteristics will be analyzed descriptively. All primary and secondary outcomes will be compared in pre-post analyses and between-group comparisons. Comparisons for categorical variables will be conducted by using the chi-square test (or the Fisher exact test when appropriate). For continuous variables, we will use the independent sample *t* test (if the distribution is not normal, we will use the Mann-Whitney *U* test). Student’s *t* test will be used to compare means and odds ratios (ORs), and 95% confidence intervals (CIs) will be estimated as well. ORs will be used with the data reported from the knowledge questionnaire, to establish the association between receiving or not receiving the intervention and improving or not knowing. Spearman’s correlation will be used to identify the association for test and re-test reliability. Multivariable analyses will be performed to explain the association of multiple variables with the factors significantly related to the primary outcome (such as the job profile of the pharmacy staff, and others that will be considered as relevant variables). The McNemar tests will be used to analyze the difference in scores of the competency’s questionnaire of skills and attitudes and the scores of the knowledge questionnaire. All statistical tests will be computed using the Statistical Package for the Social Sciences (version 23; SPSS, Chicago, IL, USA) with significance defined as a *p* < 0.05.

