## Trial design

A multicenter, prospective, parallel-group, cluster-randomized controlled, superiority trial will be conducted (see Figs. 1 and 2). The study will be carried out over 12 months (1 year) of intervention (i.e., the continuing education program) delivery and follow-up. Drugstores and drugstores/pharmacies (the clusters) will be randomized at a 1:1 ratio to enroll in either the intervention group or the control group. The geography zone (neighborhoods) will be randomized stratified.

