### Sample size

A study carried out in Spain evaluated the competences pharmacists, principally the knowledge before and after an educational intervention facilitated by pharmacists, finding that the intervention increases in 37% the knowledge of the pharmacists who attended the course [23]. Therefore, the continuing education program is expected to improve the pharmacy staff competencies in the intervention group at least 30% and in the control group by 15% (less in improving or increasing competencies). With a confidence level of 95% and a power of 80% and superiority design, it was calculated that it is necessary to include at least 121 drugstores or drugstores/pharmacies in each group. To cover losses to follow-up, the sample was increased by 10%, increasing the sensitivity for the fulfillment of secondary objectives; the size of the final sample will be 135 drugstores or drugstores/pharmacies for each group (1:1 ratio).

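### Patient satisfaction is an ordered rating, but the analysis rule has no ordinal route and on its plain reading sends it to chi-square, which ignores order and direction

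*Protocol article*

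**What the plan says.** The section on satisfaction of patients or caregivers states "The satisfaction of the care received in drugstores or drugstores/pharmacies will be evaluated with a 5-point scale ranging from excellent". The labels that follow run down to bad; counting excellent there are six, although the scale is called 5-point.

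Statistical methods compares every primary and secondary outcome before and after and between groups, and gives two routes:
- Categorical: "Comparisons for categorical variables will be conducted by using the chi-square test (or the Fisher exact test when appropriate").
- Continuous: "For continuous variables, we will use the independent sample" t test, with Mann-Whitney if the distribution is not normal.

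Ordered categories get no method of their own, and the section does not say which route the satisfaction rating takes. The only outcome for which it gives odds ratios a specific use is the knowledge questionnaire.

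Under Trial design, "A multicenter, prospective, parallel-group, cluster-randomized controlled, superiority trial will be conducted". Objectives lists satisfaction of patients and caregivers as the third objective.

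**The concern.** A single item answered in ordered words is not a continuous variable, so the written rule most naturally takes it to chi-square. Two things follow.

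- **Order is discarded.** A general move towards better ratings is spread over 4 degrees of freedom (five levels) or 5 (six levels) instead of being tested on one. A real improvement is more likely to be missed.
- **Direction is lost.** A significant result says only that the two distributions differ. It can arise when one arm has more ratings at both ends and no net gain, which does not answer a superiority question. No effect measure is named for this rating that would supply the direction.

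The outcome matters because Secondary outcomes measures process characterization and service implementation at T0 only, and staff satisfaction in the intervention arm only. Patient satisfaction is the one secondary outcome that can be compared between arms after the programme.

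**Working it through.** **1. The plan's own figure.** No power is stated for satisfaction; the only calculation concerns competencies. Inputs from Sample size: "With a confidence level of 95% and a power of 80% and superiority design", with improvement "in the intervention group at least 30% and in the control group by 15"%. Taking alpha as two-sided 0.05 (sidedness is not stated), with pooled variance and mean proportion 0.225:

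n = [1.960 × √(2 × 0.225 × 0.775) + 0.842 × √(0.15 × 0.85 + 0.30 × 0.70)]² / 0.15² = (1.157 + 0.489)² / 0.0225 ≈ 120.5, so 121 per group.

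Allowing for 10% losses, 121 / 0.90 = 134.4, so 135. Both stated figures reproduce: "it is necessary to include at least 121 drugstores or drugstores/pharmacies in each group" and "the size of the final sample will be 135 drugstores or drugstores/pharmacies for each group (1:1 ratio").

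**2. Number of ratings.** At least three patients or caregivers per pharmacy gives at least 135 × 3 = 405 ratings per arm. With within-pharmacy correlation ρ the design effect is 1 + 2ρ, so the effective number lies between 405 (ρ = 0) and 405 / 3 = 135 (ρ = 1). The documents do not give ρ.

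**3. Power at equal noncentrality.** Under a uniform shift a 1-df ordinal test and the Pearson chi-square have about the same noncentrality; the chi-square spreads it over more degrees of freedom. For 80% power at 1 df, λ = (1.960 + 0.842)² = 7.85. Noncentral chi-square power at the same λ, repeated for other reference powers:

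| Ordinal test, 1 df | Chi-square, 4 df (five levels) | Chi-square, 5 df (six levels) |
|---|---|---|
| 50% | 30.8% | 28.1% |
| 80% | 59.5% | 55.5% |
| 90% | 74.0% | 70.3% |
| 95% | 83.7% | 80.6% |
| 99% | 94.8% | 93.2% |

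At the 80% reference the loss is 20.5 or 24.5 points. To regain 80%, chi-square needs λ = 11.94 (4 df) or 12.83 (5 df): 11.94 / 7.85 = 1.52 or 12.83 / 7.85 = 1.63 times the ratings.

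**4. Simulation over assumed effects.** The documents give no distribution or effect, so these inputs are assumptions: five or six levels, evenly spread or skewed towards good ratings (30/35/20/10/5% or 20/30/25/15/7/3%), a common odds ratio (OR) from 1.2 to 2.0, independent ratings, and 4,000 runs per setting. Pearson chi-square is compared with tie-corrected Mann-Whitney.

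| OR | Points lost by chi-square, 405 per arm | Points lost, 135 effective per arm |
|---|---|---|
| 1.2 | 12 to 16 | 4 to 5 |
| 1.3 | 20 to 25 | 8 to 12 |
| 1.4 | 21 to 26 | 15 to 17 |
| 1.5 | 16 to 20 | 18 to 21 |
| 1.7 | 5 to 7 | 22 to 26 |
| 2.0 | under 1 | 17 to 22 |

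Example: five even levels, OR 1.4, 405 per arm: chi-square 56%, Mann-Whitney 77%.

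**5. Effects that are not a uniform shift (405 per arm).**
- Only the top two categories change (30/35/20/10/5% becomes 40/25/20/10/5%): chi-square 83%, Mann-Whitney 38%. Here chi-square does better.
- More ratings at both ends with no net shift (20% in each category becomes 25/15/20/15/25%): chi-square is significant in 74% of runs, Mann-Whitney in 5.5%. This is the lack of direction in numbers.

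**The case against.** A reader might infer that the protocol prescribes chi-square for satisfaction and that the trial therefore gives up 20 points of power. The documents support neither statement. Statistical methods never names a test for this item. The instrument is described as a points scale, and questionnaire results are elsewhere called scores; if the rating were scored and treated as continuous, the same section would lead to Mann-Whitney, which uses the order. The 20 points need a uniform shift, independent ratings and an ordinal test near 80% power, and no document states any of these. If ratings were dichotomised, chi-square would have 1 df and the calculation above would not apply.

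It can also be said that this is detail for an analysis plan that is not shown, that chi-square on ordered categories is a valid test apart from clustering, and that direction can be read from the tabulated ratings.

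These points limit the claim but do not remove it. The article does not stay silent: it states a rule for all outcomes, and for ordered words the plain reading of that rule is the categorical route. Mann-Whitney enters only as a fallback for non-normal continuous data, and no cut-point for dichotomising is given. At the least, the choice between tests that can differ by more than 20 points of power is left open. That chi-square wins in some settings is a reason to fix the test in advance.

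**Conclusion.** The point holds in a conditional form. The stated rule has no place for an ordered rating, and its plain reading applies a test without order or direction to the only secondary outcome comparable between arms at T12. Under a uniform proportional-odds shift detectable with 80% power by an ordinal test, chi-square has about 60% power with five levels or 56% with six. Over the other assumed effects the loss runs from under 1 to about 26 points, and the ranking reverses for some non-uniform effects. A flat 20-point loss should not be quoted as a property of this trial.

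The simulated powers treat ratings as independent, while at least three come from each randomised pharmacy. That is a separate matter which affects both named tests, so a plain Mann-Whitney is not a full remedy. The outcome is secondary and the primary analysis is untouched. The change should be made, but the trial does not stand or fall on it.

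**What to change.** In Statistical methods, state that the satisfaction rating, and any other ordered-category item compared between arms, is analysed as ordinal. A proportional-odds model for arm is preferable, reporting a common odds ratio with 95% CI and using cluster-robust errors or a random effect for pharmacy. Limit chi-square and Fisher to unordered or yes/no variables. In the section on satisfaction of patients or caregivers, reconcile the stated five points with the six labels.

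The cost is a sentence or two of wording before the T12 ratings are analysed, with no new data. SPSS 23, the named software, fits ordinal models; the team should confirm that its installation carries the chosen allowance for pharmacy. The small downside is the proportional-odds assumption, which should be checked and the rating distribution tabulated by arm.

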##### Pharmacy staff

The study will recruit at least one pharmacy staff member from each drugstore or drugstore/pharmacy (professional, technological, technical, or Drug Dealer). To be included in the study, the pharmacy staff will have to meet the following criteria: (a) work in the drugstores or drugstores/pharmacies and (b) have access to a computer and the Internet.

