#### Patients or caregivers

At least three patients or caregivers from each drugstore or drugstore/pharmacy will be recruited who had previously been dispensed with medication by the pharmacy staff of each drugstore or drugstore/pharmacy. The researchers will inform the potential candidates (patients or caregivers) about the study and will ask for their authorization to participate; they will be registered and will sign a consent form. The variables related to the objectives of the study in the case of the patients who agree to participate will be assessed. The patients will not receive any compensation for participating in the study.

One of the researchers will make visits to the pharmacy staff. The visits will be organized according to the geographical distribution where the drugstores and drugstores/pharmacies are located. The researcher will enter the drugstores or drugstores/pharmacies and remain there for as long as necessary to interview a minimum of 3 patients or caregivers who enter the drugstores or drugstores/pharmacies requesting the drug dispensing process. Patients or caregivers will be selected in order of arrival or admission to the drugstores or drugstores/pharmacies. The researcher will approach the patient or caregiver and invite them to participate in the study. If the patient or caregiver agrees, they will sign the informed consent, and they will be interviewed to complete the measurement questionnaire. There will be no selection criteria related to the characteristics of the patient or caregiver, nor of the medications dispensed.

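### Patient satisfaction, measured on at least three people per randomised pharmacy, is compared between arms with tests that make no allowance for clustering

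*Protocol article*

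**What the plan says.** All of the relevant text is in the protocol article.

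- **Unit of randomisation** (Trial design): "Drugstores and drugstores/pharmacies (the clusters) will be randomized at a 1:1 ratio".
- **Patients per pharmacy** (Recruitment, Patients or caregivers): "At least three patients or caregivers from each drugstore or drugstore/pharmacy will be recruited". They are taken in order of arrival, and no maximum is set.
- **Staff per pharmacy** (Inclusion criteria, Pharmacy staff): "The study will recruit at least one pharmacy staff member from each drugstore or drugstore/pharmacy". Again no maximum is set.
- **Patient outcome** (Secondary outcomes): "Level of satisfaction of patients or caregivers with ambulatory (outpatient) pharmacy services", measured at baseline (T0) and at 12 months (T12).
- **Scope of the analysis** (Statistical methods): "All primary and secondary outcomes will be compared in pre-post analyses and between-group comparisons".
- **Tests** (Statistical methods): "Comparisons for categorical variables will be conducted by using the chi-square test (or the Fisher exact test when appropriate". For the other type of variable, "For continuous variables, we will use the independent sample" t test, or the Mann-Whitney test if the distribution is not normal. Odds ratios and 95% confidence intervals are added, "with significance defined as a" p-value below 0.05.

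The article mentions no ICC, design effect, random effect, GEE, cluster-robust variance or pharmacy-level summary.

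**The concern.** Patients interviewed in one pharmacy rate the service of the same establishment, usually given by the same few people, so their answers are likely to be correlated. The trial's own rationale, that better-trained staff produce more satisfied patients, assumes as much. The named two-sample tests treat every observation as independent. Used on individual patients, they count three correlated answers as three full units of information, although the treatment was assigned once, to the pharmacy.

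The error goes in one direction. It makes it easier to declare that the programme improved patient satisfaction when it did not, and it overstates the precision of any difference reported. This is not a detail left to a fuller document: the article names the tests, the software and the significance level, and the named tests do not fit the stated design.

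**Working it through.** **1. The plan's own sample size.** Inputs from Sample size: 30% versus 15%, 95% confidence, 80% power. The two-sided pooled formula for two proportions, without continuity correction, gives

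n = [1.96·√(2 × 0.225 × 0.775) + 0.8416·√(0.30 × 0.70 + 0.15 × 0.85)]² / 0.15² = (1.1575 + 0.4889)² / 0.0225 ≈ 120.5, so 121 per group.

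Allowing for 10% loss, 121 / 0.90 = 134.4, so 135. Both stated figures reproduce. They are counted in pharmacies and correspond to one observation per pharmacy.

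**2. Patients: inputs.** m = 3 per pharmacy (the stated minimum) and 135 pharmacies per arm, hence 405 patients per arm. The ICC is not given. A range of 0.01 to 0.30 is assumed.

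**3. Formulas.** Design effect DE = 1 + (m − 1) × ICC. True two-sided error of a nominal 5% test = 2 × [1 − Φ(1.96 / √DE)]. Width of the naive interval relative to the correct one = 1 / √DE. Effective sample size = 405 / DE.

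Example at ICC 0.10: DE = 1 + 2 × 0.10 = 1.20; 1.96 / √1.20 = 1.789; error = 7.4%; relative width = 0.91; effective size = 405 / 1.20 ≈ 338.

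| ICC (assumed) | DE | True error | Naive / correct width | Effective n per arm |
|---|---|---|---|---|
| 0.01 | 1.02 | 5.2% | 0.99 | 397 |
| 0.05 | 1.10 | 6.2% | 0.95 | 368 |
| 0.10 | 1.20 | 7.4% | 0.91 | 338 |
| 0.20 | 1.40 | 9.8% | 0.85 | 289 |
| 0.30 | 1.60 | 12.1% | 0.79 | 253 |

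Three is a minimum. With five patients per pharmacy the error is 7.4% at ICC 0.05 and 14.4% at ICC 0.20.

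**4. Check by simulation.** Beta-binomial data with no treatment effect, 135 pharmacies per arm, three patients each and 20,000 runs: the chi-square test without continuity correction rejected in 6.8%, 7.9% and 10.3% of runs at ICC 0.05, 0.10 and 0.20. With one observation per pharmacy it rejected in 4.5%. A separate simulation with 121 pharmacies per arm (4,000 runs) gave 6.7%, 7.7%, 9.6% and 12.2% at ICC 0.05, 0.10, 0.20 and 0.30, while a t test on pharmacy totals stayed at 4.9% to 5.3%.

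**5. Staff.** With m = 1, DE = 1 at any ICC and the error is 5.0%. With m = 2 in every pharmacy, the error is 5.6%, 6.2%, 7.4% and 8.6% at ICC 0.05, 0.10, 0.20 and 0.30.

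**6. Pre-post comparison of patients within an arm.** If an unpaired test is used and the pharmacy effects at T0 and T12 have correlation r, the ratio of the true to the assumed variance is 1 + (m − 1) × ICC − m × ICC × r. With m = 3 this is 1 + ICC × (2 − 3r), which falls below 1 once r exceeds 2/3. The article gives no value for r.

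**The case against.** The strongest reply is that Statistical methods never states the unit of analysis. A t test or Mann-Whitney test on one summary value per pharmacy is a valid cluster analysis, and the simulation above relies on exactly that. The section also lists McNemar tests and multivariable analyses. The first part stands as a limit on the wording: the article does not say that individuals are the unit, so the inflation is conditional on patient-level use. It does not remove the point. Chi-square and Fisher tests work on counts of individual responses, and nothing directs the analyst to summarise by pharmacy first. McNemar tests are named for the staff questionnaires, and the multivariable analyses are described as exploring factors related to the primary outcome. Neither deals with clustering of patients.

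A second reply is that the effect is small at low ICC. That is correct: 5.2% at 0.01 and 6.2% at 0.05 with three patients. The 10% to 12% figures need an ICC of 0.20 to 0.30.

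A reader might infer three stronger things, which the article does not support.

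- **That the primary result is inflated.** Staff competencies are affected only where a pharmacy enrols more than one person. The sample size matches one observation per pharmacy, and the earlier survey described in the Discussion interviewed as many staff as pharmacies. The recruitment rule permits more, but no passage plans it.
- **That the 121 pharmacies per group need a design effect.** With one staff member each, they do not.
- **That ignoring the link between T0 and T12 patients adds to the inflation.** That the two samples are different people is likely from recruitment by order of arrival, but it is not stated. Step 6 shows that ignoring the link can make an unpaired pre-post test conservative.

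**Conclusion.** The point holds for the between-arm comparison of patient and caregiver satisfaction, a secondary outcome. Every pharmacy supplies at least three observations, so patient-level use of the named tests is anticonservative for any positive ICC. The size rests on an assumed ICC of 0.01 to 0.30, three patients in every pharmacy and the normal approximation; larger numbers per pharmacy make it worse.

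For the primary staff outcomes the point is conditional: no inflation with exactly one person per pharmacy, and about 5.6% to 8.6% if every pharmacy supplied two and the ICC lay between 0.05 and 0.30. It is a correctable mismatch between design and analysis, not evidence that the primary comparison is invalid.

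**What to change.** Amend Statistical methods as follows.

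- **Patient satisfaction between arms:** compare pharmacy-level means or proportions, or fit a mixed model or GEE with pharmacy as the cluster. If T0 and T12 are modelled together, include an arm-by-time term.
- **Between-arm staff outcomes:** apply the same approach if any pharmacy contributes more than one staff member. If every pharmacy contributes exactly one, say so; a pharmacy random effect at a single time point is then neither needed nor separable from residual error.
- **Staff satisfaction with the programme:** no change for this reason, since it is measured in the intervention arm only and has no between-arm comparison.

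The change needs no new data. Trial status describes the study as still in intervention and follow-up, so the text can be settled before the final analysis. The price is somewhat wider intervals for patient satisfaction: by the factor √DE, from about 1% wider at ICC 0.01 (√1.02 ≈ 1.01) to about 26% wider at ICC 0.30 (√1.60 ≈ 1.26).
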